### Study aims

The specific objectives of the current study are:*Process evaluation* to investigate the internal and external validity of the intervention based on sampling quality (recruitment, randomization, and reach) and intervention quality (relevance, feasibility, and performance according to protocol). The process evaluation will be conducted prior to the effect evaluation in order to provide essential information about credibility and generalizability [24].*Effect evaluation* to assess whether ‘Partner in Sight’ is superior to a pseudo-intervention and control group in terms of producing a clinically significant increase in subjective well-being, as proven by an increase in caregivers’ sense of competence, perceived control, momentary positive affect, and a decrease in psychological complaints (depression, anxiety, stress, and momentary negative affect). A follow-up evaluation will be conducted to examine whether the effects have lasted two and six months after the intervention.*Economic evaluation* to assess the cost-effectiveness of ‘Partner in Sight’ by estimating the impact of the intervention on resource use, costs, and health outcomes.

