### Sample size

The calculation of the sample size will be based on previous studies using the Sense of Competence Questionnaire (SCQ) as outcome measure in intervention studies for caregivers of PwD, the use of repeated measures, within-between interaction with a mean effect size of 0.8 [48], and the following assumptions: alpha 0.05, 80 % power and 25 % loss to follow up. Accordingly, we aim to enrol 90 participants in the study (30 participants per group).

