### Statistical analyses

#### Primary and secondary outcome measures

Data will be entered twice to guarantee data integrity. Before the analyses, data will be checked for missing values and handled according to their distribution (missing completely at random, missing at random, or not missing at random), and the ‘intention-to-treat’ principle. Additionally, data will be checked for outliers, and normality. Non-parametric tests will be used in case of non-normality after data transformation. Possible baseline differences in group characteristics will be tested with t-tests for continuous and *χ*^2^-tests for categorical variables.

To investigate changes in the primary and secondary outcomes for each group during the intervention period, an analysis of covariance (ANCOVA) will be performed with outcome at post-intervention as the dependent variable, group (experimental, pseudo-experimental, control) as the between-subject factor, and outcome at baseline and potential confounders (e.g. demographic variables, coping, personality, and quality of the relationship) as covariates. Separate analyses will be conducted for each outcome variable. Group differences in the post-intervention outcome, adjusted for the baseline value, will be examined to test the effectiveness of the intervention. In case group differences are present, the inter-group effect size will be calculated using Cohen’s *d*.

To examine changes in the primary and secondary outcomes for each group during the total study period, a linear mixed model (LMM) for repeated measures will be conducted. Analyses will be performed with group as a fixed between-subject factor (3 levels: experimental, pseudo-experimental, and control group) and time as fixed within-subject variable (4 levels: baseline, post-intervention, two-month follow-up, and six-month follow-up) and first-order interactions as additional fixed factors. The LMM will estimate fixed effects (regression slopes) for change in the intervals during (T0-T1) and after (T1-T2, T2-T3) the intervention period. The intervals will be entered as a categorical dummy variable (3 levels). Potential confounders will be added to the model as covariates. Additionally, coach will be added as a random factor to estimate the variability ascribed to the coach.

All data will be analysed using STATA 12.1 [49]. Tests of significance will report mean change and will be two tailed with *α* set at 0.05.

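### The follow-up aim asks whether the group effect is still there at two and six months, but the effects named for the mixed model are changes within successive intervals, which do not answer it directly

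*Protocol article*

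**What the plan says.** Study aims (Protocol article) defines the effect as superiority of the intervention over the pseudo-intervention and the control group. It adds a follow-up evaluation to "examine whether the effects have lasted two and six months after the intervention".

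Statistical analyses, Primary and secondary outcome measures, gives two analyses.

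- An ANCOVA at T1: "Group differences in the post-intervention outcome, adjusted for the baseline value, will be examined to test the effectiveness of the intervention".
- A linear mixed model over all four visits, with group (three levels), "time as fixed within-subject variable (4 levels: baseline, post-intervention, two-month follow-up, and six-month follow-up) and first-order interactions as additional fixed factors". The effects to be estimated are then named: "The LMM will estimate fixed effects (regression slopes) for change in the intervals during (T0-T1) and after (T1-T2, T2-T3) the intervention period". Their coding follows: "The intervals will be entered as a categorical dummy variable (3 levels", where the bracket closes.

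The section ends with "Tests of significance will report mean change and will be two tailed". It names no group difference at T2 or T3, and no group difference in change from T0 to T2 or from T0 to T3.

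Sample size assumes a "within-between interaction with a mean effect size of 0.8" and "alpha 0.05, 80 % power and 25 % loss to follow up", giving 90 participants, 30 per group.

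**The concern.** Whether an effect has lasted is a question about the size of the group difference at T2 and T3. The named follow-up effects answer another question: did the groups move apart or together after T1? A null group term for T1-T2 or T2-T3 says only that no further relative change was shown. A significant negative term says that some benefit was lost, not that none is left.

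A stated aim therefore has no declared estimate that answers it directly. With 30 per arm before losses, the gap matters. Interval changes are imprecise, and anyone who tries to judge durability from them alone has little to go on.

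**Working it through.** **1. Aim and declared estimates side by side**

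| Question | Estimate named in the plan |
|---|---|
| Group difference at T1 | ANCOVA at T1, baseline-adjusted |
| Group difference remaining at T2 | none named; T1-T2 slope only |
| Group difference remaining at T3 | none named; T2-T3 slope only |

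**2. What the interval terms contain**

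Let D(t) be the group difference in mean change from T0 to visit t. The three interval terms are

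- I1 = D(T1)
- I2 = D(T2) − D(T1)
- I3 = D(T3) − D(T2)

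Hence D(T2) = I1 + I2 and D(T3) = I1 + I2 + I3. I2 and I3 do not depend on the level of D. An effect kept at 0.8 SD and no effect at any visit both give I2 = I3 = 0. The durability quantities are sums of the interval terms, so the fitted model contains them, but the plan does not list them.

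**3. How much the follow-up interval tests can show**

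The plan gives no figure for the follow-up tests to reproduce. Its total of 90 cannot be re-derived without a within-person correlation and the metric of the effect size, neither of which is stated; this point does not depend on it.

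Inputs from the plan:

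- 30 per arm, and about 22 after 25% loss (30 × 0.75 = 22.5)
- two-sided alpha 0.05
- effect 0.8, read here as a standardised difference

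Assumptions: SD 1 at every visit; equal correlation r between visits of 0.3, 0.5 or 0.7; and a group difference of 0.8 at T1, 0.4 at T2 and 0 at T3, so that I2 = I3 = −0.4.

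The standard error of a between-arm difference in change is SE = √(2(1 − r)) × √(2/n). For n = 22 and r = 0.5 it is 1.000 × 0.302 = 0.302. Approximate power for a change of 0.4 is Φ(0.4/SE − 1.96) = Φ(1.33 − 1.96) = 26%, so one interval test misses the fade in about 74% of trials. The last three columns come from a simulation of 40,000 two-arm trials per row, using t-tests.

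| n per arm | r | SE | Power, one interval (formula) | Power, one interval (simulated) | Neither T1-T2 nor T2-T3 significant | Same, among trials with a significant T0-T1 effect |
|---|---|---|---|---|---|---|
| 22 | 0.3 | 0.357 | 20% | 19% | 62% | 54% |
| 22 | 0.5 | 0.302 | 26% | 26% | 51% | 45% |
| 22 | 0.7 | 0.234 | 40% | 39% | 31% | 29% |
| 30 | 0.3 | 0.306 | 26% | 25% | 52% | 46% |
| 30 | 0.5 | 0.258 | 34% | 33% | 39% | 35% |
| 30 | 0.7 | 0.200 | 52% | 50% | 17% | 17% |

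If the effect is truly kept at 0.8, neither interval test is significant in about 91% of trials. Two non-significant interval tests are therefore common whether the effect was kept or lost.

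**4. The contrast that matches the aim**

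Under the same full fade, D(T3) = 0.8 − 0.4 − 0.4 = 0, and the T0-T3 group contrast is significant in about 5% of trials, its nominal level. If 0.8 is kept, it is significant in 59% / 74% / 92% (22 per arm) or 73% / 86% / 98% (30 per arm) at r = 0.3 / 0.5 / 0.7. It separates a kept effect from a vanished one.

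**The case against.** - *The model already holds the answer.* This stands. Group by four-level time with interactions is saturated in the means, so the T0-T2 and T0-T3 contrasts are linear combinations of its coefficients. The point is limited to what is named.
- *The choice of contrasts belongs in the analysis plan.* Often so. Here, however, the article does not leave the matter open: it names the effects to be estimated, and they do not match its own aim.
- *A reader might infer that a faded effect will be reported as lasting.* The document does not support that. It nowhere says that a non-significant interval slope will be taken as durability, and it says mean change will be reported, so expected estimates of −0.4 SD per interval would be visible. The miss rates are those of an assumed reading rule.
- *A reader might also infer two conflicting time variables.* Four visits give three intervals, and successive-difference terms can simply recode four-level time with the same fit. The wording is loose but need not be contradictory.
- *The scenario is selected.* True. If all benefit is lost by T2 (r = 0.5), then among trials with a significant T0-T1 effect only 17% (22 per arm) or 9% (30 per arm) go unflagged. A joint two-degree-of-freedom test of both follow-up terms, which the plan does not name, would miss the even fade in 34% (r = 0.5) or 12% (r = 0.7) at 22 per arm. On the same large-sample footing, the two separate tests miss it in 49% and 28%.
- *Interval change bears on maintenance.* It does, once a T1 effect is established. It supports the durability estimate but cannot replace it.

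**Conclusion.** The point holds as a mismatch between a stated aim and the estimates declared for it. No named estimate says directly whether a group difference remains at two or six months, although the specified model can produce one. The T1 effectiveness test is unaffected.

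The size is illustrative. Under the assumed even fade, and only if the two interval tests were the sole basis for judging durability, the complete loss of the effect would go unflagged in 17% to 62% of trials over 22 to 30 per arm and correlations of 0.3 to 0.7. The correlation, equal SDs, fade path and reading rule are all assumptions. The mismatch itself rests on none of them.

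**What to change.** Keep the mixed model and change the wording around it.

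1. Name as the durability estimates the group differences in change from T0 to T2 and from T0 to T3, for experimental versus control and experimental versus pseudo-experimental, each with a 95% interval. Defining them as change from T0 settles how baseline enters a model that keeps it as an outcome level.
2. Report the T1-T2 and T2-T3 slopes as supporting description.
3. State that the three interval terms are a coding of four-level time and not a second time variable.

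No new data or participants are needed. The cost is more reporting: four contrasts per outcome, or 20 over the five questionnaire outcomes (SSCQ, PMS, CES-D, PSS, HADS-A). Precision also stays limited. At r = 0.5 the 95% half-width is about 1.96 × 0.302 = 0.59 SD with 22 per arm, or 1.96 × 0.258 = 0.51 SD with 30. A half-faded difference of 0.4 SD at T2 would reach significance in only about 25% or 33% of trials. The plan should therefore say that durability is judged from the estimates and their intervals, not from significance alone.

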#### ESM outcome measures

Subjects have to complete at least 33 % of the ESM beeps in order to be included in the ESM data analysis [4]. To investigate changes in momentary positive and negative affect between the 3-day ESM baseline and post measurement for each group, an LMM will be performed for both outcome measures. LMMs are ideally suited for ESM data, since these models take into account the hierarchical data structure in which multiple ESM observations (beep level 1) are nested within days (day level 2), and days are nested within subjects (subject level 3). The XTMIXED command in STATA 12.1 [49] will be used to conduct analyses with group (3 levels: experimental, pseudo-experimental, and control group), time (2 levels: baseline and post-intervention), and the two-way interaction between group and time as fixed factors. Random slopes, representing positive or negative affect, will be added at the subject, day, and beep level. Potential confounders will be included in the model as covariates.

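### Confounders added as plain covariates to the two mixed models leave the group-by-time effects essentially unadjusted if they are time-fixed, and adjust for post-randomisation variables if they are time-varying

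*Protocol article*

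**What the plan says.** All references are to the protocol article.

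- **Follow-up mixed model** (Statistical analyses, Primary and secondary outcome measures). Fixed factors are group (3 levels) and time (4 levels, baseline included) "and first-order interactions as additional fixed factors". The target is change: "The LMM will estimate fixed effects (regression slopes) for change in the intervals during (T0-T1) and after (T1-T2, T2-T3) the intervention period". Then: "Potential confounders will be added to the model as covariates".
- **ESM mixed model** (Statistical analyses, ESM outcome measures). Fixed factors are group, time (baseline and post-intervention) and their two-way interaction. Then: "Potential confounders will be included in the model as covariates".
- **Post-intervention ANCOVA** (same section as the follow-up model). The T1 outcome is regressed on group, the T0 outcome and potential confounders. The examples given are demographics, coping, personality and quality of the relationship.
- **Schedule** (Table 2). Demographics are collected at T0 only; the Additional measures section places dementia severity among them. Coping, neuroticism and relationship quality are measured at T0, T1, T2 and T3.
- **Size** (Sample size). "we aim to enrol 90 participants in the study (30 participants per group"), with 25% loss to follow-up assumed.

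**The concern.** When baseline is one of the outcome visits and the effect is a difference in change, a covariate helps only if its association with the outcome may differ between visits. That requires a covariate-by-time term, and neither model description names one. The same confounders do adjust in the T1 ANCOVA, so the plan's two analyses of T0-T1 would differ in what they adjust for.

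The ANCOVA does not cover the rest. It stops at T1 and is described for the primary and secondary outcomes. The two- and six-month effects, a stated study aim, come only from the follow-up mixed model. Momentary positive and negative affect, listed among the main outcomes in the abstract, come only from the ESM model. For these results the covariate sentence is the only adjustment described. With 30 per arm, entry open to all dementia subtypes and stages, and block randomisation without any described stratification, chance imbalance is a fair worry.

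**Working it through.** The plan gives no figure on this point, so there is none to reproduce. The claim is structural; the sizes below rest on assumptions, which are named.

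**1. Algebra.** Let x_i be a covariate with one value per caregiver, and let the mean be E[Y_it] = mu_gt + beta·x_i, with a free mean for each group and visit. With complete data and a within-person covariance common to all caregivers, the fitted mean is

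mu_gt = Ybar_gt − beta·xbar_g.

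The change from T0 is

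mu_gt − mu_g0 = (Ybar_gt − beta·xbar_g) − (Ybar_g0 − beta·xbar_g) = Ybar_gt − Ybar_g0.

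Beta has dropped out. The same holds for T1-T2, T2-T3 and any group difference in these changes. Adding gamma_t·x_i (covariate by time) gives each visit its own slope, and x then stays in the contrast.

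**2. Numerical check.** Simulated trials with three arms of 30 and no true treatment effect; x was shifted by 0.5 SD between arms and also affected change. Entries are the mean spurious group-by-time estimate, in the simulation's own outcome units.

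| Setting | No covariate | x as main effect | x and x-by-time |
|---|---|---|---|
| Four visits, complete data (last visit) | 0.434 | 0.434 | −0.077 |
| Four visits, about 20-25% dropout depending on x (last visit) | 0.451 | 0.465 | −0.027 |
| ESM, beeps within days within caregivers, 4-10 beeps a day | 0.132 | 0.132 | 0.032 |

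With complete data the largest difference between the first two columns in any trial was 4e-14. With dropout the main effect moved the estimate by 0.066 on average and 0.207 at most, against a contrast SD of about 0.80. In the ESM runs the largest shift was 0.007.

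**3. Precision.** If x correlates rho with change within arms, covariate-by-time multiplies the contrast variance by about 1 − rho². For rho = 0.3 the saving is 0.09 (9%); for rho = 0.5 it is 0.25 (25%). A simulation at rho = 0.4 gave a T0-T1 contrast SD of 0.233 without the covariate, 0.233 with its main effect and 0.214 with covariate-by-time. (0.214/0.233)² = 0.84, a saving of 16%, which matches 0.4² = 0.16.

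**4. Chance imbalance.** The standard error of a difference in covariate means between two arms of 30 is sqrt(2/30) = 0.258 SD.

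- Imbalance of 1 SE: 0.258 × 0.3 = 0.08 to 0.258 × 0.5 = 0.13 SD of change left uncorrected.
- Imbalance of 2 SE: 0.15 to 0.26 SD.

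The range 0.3-0.5 is an assumption; the documents give no correlation.

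**5. Time-varying reading.** If coping, neuroticism or relationship quality enter with their value at each visit, they do not cancel. In a simulation where treatment was assumed to shift the covariate by 0.5, the group-by-time estimate moved from 1.50 to 0.40. The Background and Discussion themselves link positive emotions to better caregiver-patient interaction and to adaptive coping, so at least coping and relationship quality may lie on the path from intervention to outcome.

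**The case against.** The article says only that confounders enter as covariates. It does not say that they are baseline values or that only main effects are used, and it does not list the first-order interactions; that these are of group and time is the natural reading, but an inference. Three of the four example confounders are measured at every visit. A reader might therefore infer that the plan fixes baseline-only main effects, and the text does not go that far. This stands, and it is why the point covers both readings. It does not rescue the sentence: demographics and dementia severity are time-fixed on any reading, and entering the other three as time-varying exchanges one problem for another.

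It can also be said that such detail belongs in a full protocol or analysis plan not shown here. That would hold if the article were silent. It states a model specification, and as worded that specification does not deliver the adjustment.

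Finally, the harm is limited. A reader might infer that the follow-up and ESM effects are biased, or that the trial's main test is unadjusted. Neither is supported. The arms are randomised, and with no built-in imbalance the contrast without covariate-by-time averaged −0.015, close to zero; the cost was an SD of 0.854 against 0.802. For the primary and secondary outcomes, the analysis named as the test of effectiveness is the T1 ANCOVA, which does adjust. Nor is the adjustment exactly nil once data are missing, although the shifts are small.

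**Conclusion.** The point holds in a limited form. For any covariate with one value per caregiver, the adjustment described for the two mixed models cancels from the group-by-time contrasts: exactly with complete data, nearly so under the dropout and unequal beep counts simulated. The two- and six-month and momentary-affect effects would carry an adjusted label and be essentially unadjusted. Read the other way, with coping, neuroticism and relationship quality as time-varying, the models adjust for post-randomisation variables and may remove part of the effect.

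Validity under randomisation is not at stake. What is lost is about 9-25% of contrast variance, and the correction of chance imbalance worth roughly 0.08-0.13 SD of change at 1 SE. Both sizes rest on the assumed correlation of 0.3-0.5 with change; the cancellation rests on no assumed figure. This is a worthwhile and cheap correction, not a fatal flaw.

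**What to change.** In both mixed-model descriptions, replace the covariate sentence with wording such as: *A short list of covariates, fixed before unblinding and taken at their T0 values only, enters the model together with each covariate's interaction with time.* The ANCOVA can keep its covariates as plain terms, with the same list at T0 values.

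An alternative with the same aim is to model only the post-baseline outcomes, with the T0 outcome and the T0 covariates as covariates.

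The data are already collected, so the cost is one sentence per model plus degrees of freedom. With the interaction, each single-score covariate takes three extra parameters in the four-visit model and one in the ESM model. The coping list alone has seven subscales: 7 × 3 = 21 interaction parameters in the four-visit model, against about 67 completers (90 × 0.75 = 67.5). The list must therefore stay short.

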#### ESM outcome measures

Subjects have to complete at least 33 % of the ESM beeps in order to be included in the ESM data analysis [4]. To investigate changes in momentary positive and negative affect between the 3-day ESM baseline and post measurement for each group, an LMM will be performed for both outcome measures. LMMs are ideally suited for ESM data, since these models take into account the hierarchical data structure in which multiple ESM observations (beep level 1) are nested within days (day level 2), and days are nested within subjects (subject level 3). The XTMIXED command in STATA 12.1 [49] will be used to conduct analyses with group (3 levels: experimental, pseudo-experimental, and control group), time (2 levels: baseline and post-intervention), and the two-way interaction between group and time as fixed factors. Random slopes, representing positive or negative affect, will be added at the subject, day, and beep level. Potential confounders will be included in the model as covariates.

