### ESM procedure

ESM will be carried out using the PsyMate, an electronic touchscreen device that is specifically designed to monitor experiences and behavior in daily life and that offers the possibility to provide immediate ESM-derived feedback (www.psymate.eu). The PsyMate has been extensively studied and refined in several studies concerning psychiatric populations (e.g. psychosis and depression) [10, 13]. In a recent ESM study with spousal caregivers of PwD, the PsyMate was considered to be a user-friendly and easily accessible device ([name] et al.: Dealing with daily challenges in dementia (Deal-id study): an innovative approach to assess caregiver functioning in the flow of daily life, submitted).

The PsyMate will be programmed to generate ten beeps (sound and vibration) per day at random intervals between 7:30 AM and 10:30 PM. ESM will be used as an assessment tool during the baseline assessment (three consecutive days = 30 beeps in total) and the post assessment (three consecutive days = 30 beeps in total) to evaluate the effectiveness of the intervention. Furthermore, ESM will be used as an intervention tool during the 6-week intervention period (three consecutive days per week = 10×3×6 = 180 beeps in total). In order to include different days of the week, the PsyMate will beep alternately on Friday, Saturday, and Sunday, or Tuesday, Wednesday, and Thursday during the intervention period.

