#### ESM outcome measures

*Momentary positive and negative affect:* the ESM data collected during the 3-day ESM baseline measurement and 3-day ESM post measurement will be used to assess caregivers’ momentary positive and negative affect. Positive affect will be defined as the mean score of the items: ‘I feel cheerful’, ‘I feel relaxed’, ‘I feel enthusiastic’, and ‘I feel satisfied’. Negative affect will be defined as the mean score of the items ‘I feel insecure’, ‘I feel lonely’, ‘I feel anxious’, ‘I feel irritated’, ‘I feel down’, ‘I feel desperate’, ‘I feel tensed’, and ‘I feel confident’. A mean positive and negative affect score will be calculated for each completed beep during the day, with higher scores indicating higher levels of positive and negative affect.

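### The mixed model for momentary affect has a random part that cannot be fitted as written and does not say which predictor carries the random slope

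*Protocol article*

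**What the plan says.** Protocol article, Statistical analyses, ESM outcome measures. Each affect score gets its own model: "To investigate changes in momentary positive and negative affect between the 3-day ESM baseline and post measurement for each group, an LMM will be performed". The data hierarchy is given as "multiple ESM observations (beep level 1) are nested within days (day level 2), and days are nested within subjects (subject level 3"). Besides group, the fixed part contains "time (2 levels: baseline and post-intervention), and the two-way interaction between group and time as fixed factors". The random part is described in one sentence: "Random slopes, representing positive or negative affect, will be added at the subject, day, and beep level".

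The outcome is defined in the ESM outcome measures section under Instruments: "A mean positive and negative affect score will be calculated for each completed beep during the day". There is thus one positive and one negative score per beep.

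The random-effects sentence names no random intercept and no predictor for the slope. Nothing elsewhere in the article corrects or explains it.

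**The concern.** A random slope is the coefficient of a predictor, allowed to vary between units. The sentence gives that role to the dependent variable. It also places a random effect on the level that already holds the residual. Whoever runs the analysis must decide what was meant.

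The tested effect is group-by-time, that is, whether mean change from baseline to post differs between arms. Its standard error has to include how much caregivers differ from one another in their true change. A subject-level random slope for time supplies that term. Random intercepts for subject and day do not, because they treat all caregivers in an arm as having the same true change apart from day and beep noise.

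At stake is the false-positive rate for momentary affect. The intervention aims directly at positive affect, and the abstract counts momentary affect among the main outcomes.

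**Working it through.** The plan states no figure for this model, so there is none to reproduce. Its beep counts are consistent: 10 × 3 = 30 per assessment and 10 × 3 × 6 = 180 during the intervention.

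**Inputs from the protocol.** Three groups; two periods of three days; 10 beeps a day; one score per beep; two-sided 0.05. There are 30 per group with 25% loss, so 30 × 0.75 = 22.5, taken as 22.

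**Inputs assumed.** The protocol gives no variance components for affect. Assumed: day variance 0.10, beep variance 0.80, 7 of 10 beeps completed. The person-by-period variance t is set at 0, 0.05, 0.10 and 0.20. The true change then has SD √(2t), which is 0, 0.32, 0.45 and 0.63 points on the 7-point scale.

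**Step 1: affect as the slope variable.** Entering the outcome as its own predictor gives coefficient 1 and a residual sum of squares of zero (about 3 × 10⁻²⁸ numerically). There is nothing left to model.

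**Step 2: random effect at beep level.** A level-1 variance of 0.64 was split between a beep effect and the residual as 0/0.64, 0.20/0.44, 0.40/0.24 and 0.60/0.04. The log-likelihood was −2324.430586 each time. The two parts cannot be separated. The redundancy does not disturb the fixed effects.

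**Step 3: subject and day intercepts only, beep as residual.**

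- Variance of a day mean: s² = 0.10 + 0.80/7 = 0.214.
- True variance of one caregiver's post-minus-baseline difference: 2(s²/3 + t).
- Variance the model uses: about (2/3)(s² + 0.6t). Six day means give five within-person degrees of freedom. One carries the change (expected mean square s² + 3t) and four do not (s²), so the pooled value is about s² + 3t/5.
- Standard-error ratio: √(model variance / true variance).
- Rejection rate under the null: 2[1 − Φ(1.96 × ratio)].

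| t | True variance | Model variance | SE ratio | 1.96 × ratio | Rejection rate |
|---|---|---|---|---|---|
| 0 | 0.143 | 0.143 | 1.00 | 1.96 | 5% |
| 0.05 | 0.243 | 0.163 | 0.82 | 1.61 | 11% |
| 0.10 | 0.343 | 0.183 | 0.73 | 1.43 | 15% |
| 0.20 | 0.543 | 0.223 | 0.64 | 1.26 | 21% |

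For the three non-zero values of t, simulation of 6,000 balanced trials per scenario with 22 per arm gave the same 11%, 15% and 21%. Using the between-person variance of change gave 4.7% to 5.2%.

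**Step 4: other assumptions.** A second simulation used the 2-df group-by-time test, all 10 beeps, 22 or 30 per group, and day/beep SDs of 0.4/0.8 or 0.2/1.0, with 10,000 runs per setting.

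| SD of true change | Rejection rate without subject slope for time |
|---|---|
| 0 | 0.05 |
| 0.2 | 0.08–0.11 |
| 0.4 | 0.17–0.23 |
| 0.6 | 0.27–0.34 |
| 0.8 | 0.36–0.41 |

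With the slope, the F test rejected 0.046 to 0.053 of the time throughout. A small check with fitted REML models (120 runs, 22 per group, SD 0.6) gave 0.29 without the slope and 0.05 with it.

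**The case against.** A reader might infer that the plan leaves out the subject slope for time, and that its standard errors will therefore be too small. The document does not support that as a statement of fact. The sentence says slopes, not intercepts, and places one at subject level. Of the named main effects, group and time, only time varies within a caregiver, so a subject slope for time is a natural repair. On that reading the test holds its level. On the literal reading no model is fitted, so there is no standard error to be wrong. Only the intercept-only reading inflates the error rate, and then only if caregivers differ in their true change. This part of the objection stands, and the conclusion is conditional for that reason.

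It is also fair that the beep-level term does not bias the test, that the size of the inflation rests on assumed variances, and that Table 2 lists the ESM measures apart from the primary and secondary outcomes.

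What does not stand is that this is ordinary condensation in a journal article. The predictor for the slope and its covariance structure could be left to an analysis plan. Naming the outcome as the slope and the residual level as a random-effect level is a positive misstatement. The favourable reading also does not rescue all three levels. Each day lies wholly in one period, so a slope for time at day or beep level could only let the variance differ between periods.

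**Conclusion.** The random part is wrong on its face, and this needs no assumed figures. It names the outcome as the random slope and adds a random effect at the residual level. It also leaves open which predictor carries the slope.

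The consequence depends on how the sentence is implemented. With a subject-level slope for time, type I error is nominal and only the text needs correcting. With subject and day intercepts alone, type I error is about 11% to 21% for person-by-period variances of 0.05 to 0.20 under the first set of assumptions. It is 5% if that variance is zero. The direction holds whenever caregivers differ in true change; the size depends on variance components that the protocol does not give.

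The point is confined to momentary positive and negative affect. The ANCOVA and mixed model for the questionnaire outcomes, including the primary SSCQ and PMS, are unaffected. Severity: should-fix.

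**What to change.** Replace the random-effects sentence with a statement that the model has random intercepts for subject and for day within subject, a subject-level random slope for time (baseline versus post), and beep as the residual level. State that group-by-time is tested from this model.

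Code the six assessment days uniquely within each caregiver. If days are numbered 1 to 3 in both periods, the software will treat a baseline day and a post day as the same day.

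In the planned software, with time coded 0/1, the random part is: `|| subject: time, cov(unstructured) || day:`.

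The cost is one sentence and one line of code. Confidence intervals may be wider than under intercepts only. If caregivers do not differ in true change, the slope variance should be estimated near zero and little is lost.
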